Statistical comparisons of data on MRI outcomes will be performed differently. Voxel-wise generalized linear model (GLM) analysis will be performed to compare gray matter volumes within and between groups while controlling for age and sex. Statistical maps of comparisons in gray matter volumes will be corrected for multiple comparisons using the false discovery rate (FDR, *p* < 0.05). Similar to gray matter volumes, differences in brain responses to the WM task and functional connectivity from the resting state fMRI at baseline will be assessed between groups using the independent samples *t* test and voxel-wise GLM analysis (FSL, feat). fMRI metrics between baseline and post-treatment will be compared using the paired samples *t* test in a voxel-wise GLM. Age and sex will be added to the GLM as regressors of no interest. Correction for multiple comparisons of fMRI metrics will be performed using a corrected cluster-size threshold of *p* < 0.05. Statistical comparisons The DTI metric maps will be statistically compared within and between groups using a non-parametric permutation test with 5000 permutations. For multiple comparisons across voxels in DTI metric maps, family-wise error correction will be used with threshold-free cluster enhancement (Randomise, FSL). Whole-brain linear regression analyses will be performed to test association between metrics of cognitive function and changes in brain function and structure. This trial will enroll 50 patients with MCI and this could be a cohort with heterogeneous cognitive function. Thus, we will follow up the aforementioned analyses to evaluate brain function and structure in subgroups with different cognitive functions at baseline. We will divide patients with MCI into equal sample sizes of low-cognitive and high-cognitive function subgroups using the MoCA-K. We will compare between MRI outcomes for low-cognitive and high-cognitive function to test whether cognitive function affects brain function and structure groups, using the independent samples *t* test with identical multiple comparisons correction, as previously described.

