## Discussion

To prevent or slow the progression of dementia, it is important to manage it in its early stage (i.e., the MCI state). Unfortunately, there are no recommended medications for MCI because cholinesterase inhibitors, well-known anti-dementia drugs, have more AEs than benefits when prescribed to patients with MCI [13–16]. In this situation, acupuncture therapy can help improve the cognitive function of patients with cognitive decline [19–24]. However, studies investigating the effects of acupuncture treatment in patients with MCI have compared acupuncture to conventional anti-dementia drugs (not sham acupuncture), and usually tested single acupoint stimulation, which is not commonly used in practice to treat patients. To assess the efficacy of acupuncture in MCI, we designed a randomized, assessor-blinded, sham-controlled trial. An acupuncture treatment protocol was developed through the consensus of investigators, to reflect actual practice.

Studies have identified abnormalities in the structure and function of the brain in patients with MCI compared to age-matched healthy adults [26, 54]. The association between progression of cognitive decline and MRI metrics including Aβ and Tau in the cerebrospinal fluid and gray matter volumes in the regions of the brain is known to play a role in cognitive function [55].

In this trial, we aim to investigate differences in functional brain responses to the WM task, functional brain networks, and brain structures following acupuncture treatment in patients with MCI. In order to clarify the efficacy of acupuncture, we will compare changes in MRI metrics between the acupuncture group and sham acupuncture group, and test whether improved cognitive function is associated with changes in MRI metrics following acupuncture treatment [54]. Although a few studies have investigated structural and functional brain plasticity in patients with MCI following acupuncture stimulation [25, 26, 56], to our knowledge, our study will be the first randomized sham-controlled trial reflecting actual practice (multiple acupoints and 24 treatment sessions) using MRI.

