The limitations of the study should be noted. We adopted Streitberger sham acupuncture as a control. The Streitberger sham needle has been designed for reliable control treatment in acupuncture research [64]. However, not only the Streitberger needle, but any type of sham acupuncture has limitations. First, we cannot blind the practitioner to the treatment allocation (our trial is not a double-blinded trial). The practitioner should be aware of the treatment type, and then they will push the shaft of needle into the handle for sham acupuncture as they were trained beforehand. In order to minimize the risk of bias as much as possible, we will carefully blind the participants and assessors to acupuncture type. Second, sham acupuncture often shows large non-specific effects [64–66] and produces physiological activity [67]. A non-specific effect of sham acupuncture cannot be dismissed in this trial, but we may compare the differences in neurological mechanisms between the two groups. Thus, we may identify the acupuncture-specific pathway associated with the improvement of cognition based on the MRI results even if the total (specific plus placebo) effect is not significantly different. Third, even if we wanted to consider MCID as a primary outcome, only MCIDs in the MMSE [68, 69] and Alzheimer’s Disease Assessment Scale-Cognitive Subscale (ADAS-Cog) [70, 71] for dementia have been studied. In those studies, the duration of interventions for neurocognitive disorders was much longer than in this trial. Thus, the MCID in the DST score for MCI cannot be included in this design. For establishing the MCID, it the acupuncture needs to be used for a longer period and interviews with participants or the Delphi expert consensus method are applied. Therefore, we calculated the effect size based on a previous study [29]. To our knowledge, there are several RCTs examining acupuncture for treatment of MCI [21], but Tan et al. [29] compared acupuncture to sham control and used the DST as an outcome measurement. Although the number of participants is small, it would be an appropriate reference to our study when considering clinical relevance. Finally, we have no healthy group as a control in this trial. A previous meta-analysis [72] showed differences between brain networks in MCI and healthy participants; however, our trial focuses on investigating acupuncture-induced functional and structural brain changes, not MCI-specific characteristics of brain function/structure relative to healthy controls. Thus, we will compare brain network changes between the acupuncture and sham acupuncture groups.

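### For task fMRI and resting-state connectivity, the Statistical analysis section names no between-arm test of change, although the Discussion promises one

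*Protocol article*

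**What the plan says.** All of this is in the protocol article.

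- **Statistical analysis, between arms (fMRI):** "differences in brain responses to the WM task and functional connectivity from the resting state fMRI at baseline will be assessed between groups", by an independent-samples t test and a voxel-wise GLM.
- **Statistical analysis, over time (fMRI):** "fMRI metrics between baseline and post-treatment will be compared using the paired samples *t* test in a voxel-wise GLM". On covariates: "Age and sex will be added to the GLM as regressors of no interest". Multiplicity is handled by a corrected cluster-size threshold.
- **Statistical analysis, structural outcomes:** the plan for VBM is to "compare gray matter volumes within and between groups while controlling for age and sex". The DTI maps are likewise compared both within and between groups, by permutation test. For neither is it stated whether the between-group comparison concerns change, post-treatment values or baseline values.
- **Discussion, on the aims of the imaging:** "we will compare changes in MRI metrics between the acupuncture group and sham acupuncture group".
- **Discussion, limitations:** "Thus, we will compare brain network changes between the acupuncture and sham acupuncture groups". Also: "Thus, we may identify the acupuncture-specific pathway associated with the improvement of cognition based on the MRI results even if the total" effect does not differ significantly between the arms.

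Objective 2 of the trial is the neurological mechanism of acupuncture, based on the MRI results.

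**The concern.** Before treatment, randomised arms differ only by chance, so a between-arm test at baseline says nothing about what acupuncture does. A pre/post change within an arm does include any effect of acupuncture. It also includes practice on the working memory task, familiarity with the scanner, the passage of time and the response to being needled at all. The article's own limitations paragraph warns that sham needling often has large non-specific effects and physiological activity. Only a contrast of change between the arms removes these shared components.

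At stake is the fMRI part of Objective 2. The article hopes to read an acupuncture-specific pathway from the MRI results even if the clinical comparison is negative. In that situation the imaging contrast would carry the whole claim of specificity, and for fMRI the methods do not contain that contrast.

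**Working it through.** **Step 1. Set the text side by side.**

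| Outcome | Between-arm test in Statistical analysis | Pre/post test in Statistical analysis | Promise in Discussion |
|---|---|---|---|
| Task fMRI, resting-state connectivity | At baseline | Paired t test in a voxel-wise GLM | Change compared between arms |
| Gray matter (VBM) | Yes, time point not stated | Within groups | Change compared between arms |
| DTI | Yes, time point not stated | Within groups | Change compared between arms |

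Two further fMRI analyses are described: whole-brain regression of brain change on cognitive measures, and a comparison of low and high MoCA-K subgroups. Neither names treatment arm as the tested factor. No group-by-time term appears. The first row is therefore a contradiction between two sections of one document, and it needs no arithmetic.

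**Step 2. Number per arm for an illustration.** The article gives no power figure for imaging. Its only one is for the DST: difference 0.87, SD 0.89, 90% power, two-sided 5%.

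n per arm = 2 × (1.960 + 1.282)² × (0.89/0.87)² = 2 × 10.51 × 1.0465 ≈ 22, so 44 in total.

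22/0.9 = 24.4, so 25 per arm and 50 in total. Both stated figures reproduce by the normal approximation. I use 22 per arm as the evaluable number.

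**Step 3. What separate paired tests can show when there is no acupuncture-specific effect.** Assume the same true standardised change d (mean change divided by its SD) in both arms. The documents give no value for d, so I take 0 to 0.8. Let P be the probability that a paired t test with n = 22 (21 df, noncentrality d√22) gives two-sided p<0.05. The arms are independent, so

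- acupuncture significant and sham not: P(1 − P);
- exactly one arm significant: 2P(1 − P).

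Example at d = 0.3: P = 0.272, and 0.272 × 0.728 = 0.198.

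Simulated values (40,000 trials per row):

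| d | P | Acupuncture only | Exactly one arm | Between-arm test of change, p<0.05 |
|---|---|---|---|---|
| 0 | 0.050 | 0.048 | 0.095 | 0.049 |
| 0.2 | 0.147 | 0.125 | 0.252 | 0.048 |
| 0.3 | 0.272 | 0.198 | 0.393 | 0.048 |
| 0.5 | 0.607 | 0.237 | 0.478 | 0.050 |
| 0.8 | 0.946 | 0.049 | 0.100 | 0.047 |

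P(1 − P) cannot exceed 0.25, which it reaches at P = 0.5; d = 0.42 gives P = 0.47 and 0.25. With 25 per arm the acupuncture-only column reads 0.047, 0.134, 0.205, 0.219 and 0.030. The direct test stays near 5% throughout, half of it in acupuncture's favour.

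These figures are for one metric at an uncorrected threshold. They do not model the cluster correction that the plan specifies.

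**The case against.** **The comparison is promised elsewhere.** The Discussion makes two plain commitments to compare change between the arms, and the fMRI sentence opens by likening itself to the gray matter analysis, which is within and between groups. Loose drafting is a plausible explanation. This stands as an account of the cause. It does not remove the defect, because the section that fixes the tests, covariates and correction says something different.

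**The phrase about baseline might attach only to connectivity.** On that reading the task comparison has no stated time point, and a between-arm test of change is still not named for either outcome.

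**This is detail for a statistical analysis plan.** A bare omission would be. Here the article does name the fMRI tests, and it places the between-arm one at baseline. A fuller document may resolve this, but the published text contradicts itself.

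**Stronger readings.** A reader might infer that brain change is never tested against sham. The documents do not support that: gray matter and DTI have between-group comparisons that are not restricted to baseline, and the Discussion commits to comparing change. A reader might also infer that specificity will be declared when one arm's paired map is significant and the other's is not. No passage states such a rule. The article does not even say that the paired test is run separately by arm, and its language about the pathway is tentative. The rates in the table therefore show why such a rule would be unsafe; they are not an error rate of this plan.

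**Imaging is secondary.** This is correct. The DST analysis is an ANCOVA with group as the fixed factor and is not affected.

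**Conclusion.** The point holds for task fMRI and resting-state connectivity. The named tests are a between-arm comparison at baseline and a paired comparison over time. Together they do not compare change between acupuncture and sham, which the Discussion says will be done, and they cannot support an acupuncture-specific fMRI finding. This conclusion rests on the text alone.

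The size can only be illustrated. If specificity were read from separate paired tests, a false acupuncture-only pattern would arise in about 5% to 25% of trials, against 5% two-sided for the direct test. The range assumes 22 per arm, one metric, no multiplicity correction and an equal true change of 0 to 0.8 SD in both arms. The high end needs a change of roughly 0.3 to 0.5 SD; at 0 or 0.8 SD the rate is about 5%.

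For gray matter and DTI, what remains is only that the article does not say whether the between-group comparison is of change.

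**What to change.** In the Statistical analysis section:

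1. Make the main fMRI analysis a voxel-wise between-arm test of each participant's post-minus-baseline map (equivalently, the group-by-time contrast), for the task response and for each connectivity map. Use age and sex as regressors and the cluster correction already specified.
2. Keep the paired within-arm maps and label them descriptive.
3. State that any claim of an acupuncture-specific fMRI effect requires the between-arm contrast of change.
4. In the same edit, say whether the between-group comparisons of gray matter and DTI are of change.

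The cost is analysis wording and one subtraction per participant. It needs no new scans, patients or software, and no sample size figure changes. The wording should be settled before the imaging data are analysed by arm.

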### Randomization, allocation concealment, and blinding

Subjects will be randomly assigned to either the acupuncture or sham acupuncture group. Stratified block randomization will be used to control the influence of age and sex. An independent statistician who is not related to the intervention practice and outcome assessment will generate a random sequence using SAS® Version 9.4 (SAS Institute, Inc., Cary, NC, USA). This study will be conducted using a central randomized competitive recruitment method. Participants signing the informed consent form voluntarily and meeting the inclusion criteria will be eligible for randomization. An investigator will then assign the participants to groups based on the random sequence prepared and sent by an independent statistician via e-mail.

In this clinical trial, participants and assessors will be blinded to treatment allocation to decrease the risk of bias from the assigned acupuncture treatment group. However, practitioners will not be blinded. The participants will be informed that they will be treated either by real or sham acupuncture before they sign the informed consent form. The validity of the participants’ blinding will be assessed by an investigator who is not involved in either the patients’ allocation procedure or performance of the acupuncture treatment. The assessor will be blinded to the treatment group and prevented from speaking with the participants. Unblinding should be determined on a case-by-case basis and considered only in a critical medical emergency.

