### MRI scanning procedure

In order to evaluate neural correlates involved in improving cognitive functions following acupuncture treatment, brain imaging data will be acquired at baseline and over a 12-week period following acupuncture treatment. Imaging data will be acquired using a 3.0-T Philips Ingenia MRI scanner (Phillips Medical System, The Netherlands) at KHUGD and a 3.0-T Philips Achieva MRI scanner (Phillips Medical System) at KHUMC, both of which are equipped with a 32-channel head coil. We will use the same imaging parameters for both MRI scanners at the two sites. First, structural MRI will be recorded for standard space co-registration, and T1-weighted 3D turbo field echo sequences (repetition time (TR)/echo time (TE) = 9.9/4.6 ms, flip angle = 8°, voxel size = 1 mm isotropic) will be applied. A whole-brain T2*-weighted gradient echo blood oxygenation level-dependent (BOLD) pulse sequence (TR/TE = 2000/35 ms, flip angle = 90°, 34 axial slices, voxel size = 1.72 × 1.72 × 4.2 mm) will be used to obtain functional MRI (fMRI) data. We will use a task fMRI approach to investigate changes in brain responses to a cognitive task following acupuncture treatment. An adaptation of the WM task by Iordan et al. [34] will be used with emotional distractors. The emotional distractors are pictures depicting emotional scenes with high arousal and negative valence from the International Affective Picture System (IAPS; mean arousal and valence scales are 6.4 and 1.8, respectively) (Fig. 3). The task fMRI run will last for 8 min and 30 s for 12 tasks. The tasks will be presented visually using MRI-compatible video goggles (NordicNeuroLab, Norway). Participants will use a push-button to perform a WM task, and WM performance will be measured by the accuracy rate and response time. Two 8-min resting-state fMRI runs will also be acquired before and after the task fMRI run. Finally, diffusion-weighted images will be obtained using a spin-echo pulse sequence (TR/TE = 9125/97 ms, voxel size = 0.96 × 0.96 × 2.2 mm, 68 slices, b-value = 1000 s/mm^2^, 32 non-collinear directions).

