### Statistical analysis

In this study, statistical analyses will be performed by an independent statistician using full analysis set (FAS) and per-protocol (PP) analyses. The FAS refers to a set that is almost identical to the intention-to-treat (ITT) ideal of including all randomized subjects, but may exclude subjects who never received the treatment or missed baseline measurement after randomization. In addition, we will perform supplementary analysis of the PP analysis group. The PP analysis group refers to a set of subjects who completed the treatment originally allocated. Compliance in this study is deemed to be satisfied only by those who have undergone more than 70% of the total number of acupuncture treatments. In other words, out of the 24 treatments, participants who do not receive treatment more than 17 times are excluded from the PP analysis group because of violation of the protocol.

All demographic and baseline characteristics of participants will be presented based on descriptive analyses. Continuous data will be presented as the average and SD and analyzed using the independent two-sample *t* test or Wilcoxon rank sum test. Dichotomous data will be presented as frequency and percentile and analyzed using the chi-square test or Fisher’s exact test.

Post-test scores will be analyzed using analysis of covariance (ANCOVA), using each group as the fixed factor and baseline score with strata factors (such as sex and age) as the covariate. Within a group, the difference pre-treatment and post-treatment will be compared using the paired *t* test or Wilcoxon singed rank test for continuous data and the chi-square test or Fisher’s exact test for dichotomous data. For repeated measures outcomes, repeated measures analysis of variance (ANOVA) will be performed to compare differences between the times of measurement.

Statistical analyses of clinical outcomes will be performed using SAS® Version 9.4 (SAS Institute, Inc.). All tests will be two-sided and a *p* value <0.05 will be considered statistically significant. We will use multiple imputations for missing data.

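### Scanner model differs by site, but the MRI models name no scanner term: comparisons of levels between patients lose precision, and the low/high MoCA-K split can be confounded

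*Protocol article*

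**What the plan says.** **Scanners.** The MRI scanning procedure section lists the machines thus: "3.0-T Philips Ingenia MRI scanner (Phillips Medical System, The Netherlands) at KHUGD and a 3.0-T Philips Achieva MRI scanner (Phillips Medical System) at KHUMC". Each carries a 32-channel head coil. The harmonisation stated is: "We will use the same imaging parameters for both MRI scanners at the two sites". The MRI data analysis sections describe no scanner, site or harmonisation step.

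**Randomisation.** "Stratified block randomization will be used to control the influence of age and sex". Site is not named as a stratum. Recruitment is not split between sites in advance: "This study will be conducted using a central randomized competitive recruitment method".

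**MRI models.** Under Statistical analysis, the voxel-wise model will "compare gray matter volumes within and between groups while controlling for age and sex". For the fMRI metrics: "Age and sex will be added to the GLM as regressors of no interest". The DTI permutation test is given a number of permutations and a multiplicity correction, but no covariate.

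**Contrasts.** The same section plans these comparisons:
- arms at baseline (fMRI);
- arms for gray matter and for DTI;
- paired pre/post fMRI comparisons;
- whole-brain regressions relating cognition to changes in the brain;
- equal low and high halves on the MoCA-K.

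The Discussion adds that changes in MRI metrics will be compared between arms.

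**The concern.** Equal sequence settings do not make two scanner models equivalent. The plan sets out its MRI models in some detail and names the nuisance regressors for gray matter and fMRI. That list leaves out the technical factor which the plan's own two-scanner design creates. This is a stated choice, not merely detail left to another document.

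What is at stake depends on the contrast. When levels are compared between patients, scanner variation goes into the residual. When the groups compared were not formed by randomisation, scanner can also be associated with group membership. The MoCA-K split is such a case: if one hospital recruits more impaired patients, the low half will hold more scans from that hospital's machine, and a scanner offset will look like an effect of cognition. The imaging matters here because the second objective rests on it.

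**Working it through.** **Inputs from the protocol.** 50 patients, 25 per arm; two scanner models, one per site; age and sex as the named nuisance regressors; two-sided 5% tests.

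**Inputs not in the protocol (assumed).** Scanner offset d = 0.25, 0.5 or 1.0 within-scanner SD; share p of patients on one scanner = 50%, with 30% and 20% as alternatives; the scanner imbalance between the MoCA-K halves.

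**1. The plan's own figure.** For DST with difference 0.87, SD 0.89, 90% power and two-sided 5%: n per arm = 2 × (1.960 + 1.282)² × (0.89/0.87)² = 2 × 10.51 × 1.0465 ≈ 22, so 44 in total. Allowing 10% dropout, 44/0.9 = 48.9, i.e. 49, raised to 50 for equal arms. The stated 44 and 50 reproduce and involve no MRI quantity.

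**2. Randomised arms, comparison of levels.** Variance inflation without a scanner term is 1 + d²·p·(1 − p).

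| Offset d (SD) | p = 50% | p = 30% | p = 20% |
|---|---|---|---|
| 0.25 | 1.016 | 1.013 | 1.010 |
| 0.5 | 1.063 | 1.053 | 1.040 |
| 1.0 | 1.250 | 1.210 | 1.160 |

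At p = 50% and d = 1.0, 25 patients per arm carry the information of 25/1.25 = 20; at d = 0.5, of 25/1.0625 = 23.5.

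**3. Chance imbalance between arms.** Ignoring the age and sex blocks, the number of one scanner's patients in an arm is hypergeometric (50 patients, 25 drawn). The probability that the arms differ by at least 20 percentage points in scanner share is 26% if 25 of the 50 are on one scanner, 22% if 15 are, and 7% if 10 are. A 20-point imbalance shifts that realised contrast by 0.2 × d, i.e. 0.05, 0.10 or 0.20 SD. The shift is as likely in either direction, so its expectation is zero.

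**4. MoCA-K halves (25 v 25, not randomised).** Let the scanner shares be p₁ and p₂, averaging 50%, and let there be no true difference between the halves.
- Variance: v = 1 + d² × [p₁(1 − p₁) + p₂(1 − p₂)]/2.
- Noncentrality: (p₁ − p₂) × d / √(2v/25), referred to a two-sided 5% t test on 48 df.
- Example with 70% v 30% and d = 0.5: v = 1 + 0.25 × 0.21 = 1.0525; noncentrality = 0.20/√0.0842 = 0.69; error rate 10%.

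| Imbalance | d = 0.25 | d = 0.5 | d = 1.0 |
|---|---|---|---|
| 20 points | 5% | 6% | 10% |
| 40 points | 6% | 10% | 24% |
| 60 points | 8% | 18% | 49% |

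These are uncorrected per-voxel rates. The planned multiplicity corrections raise the threshold, but the offset is a systematic difference in means and they do not remove it.

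**5. Change contrasts.** If a patient's measurement is Y + s at both visits, with the same scanner offset s, then (Y₂ + s) − (Y₁ + s) = Y₂ − Y₁. The offset leaves paired tests, change scores compared between arms, and regressions on brain change. It remains if the scanner effect is a gain or a drift, or if the patient moves between scanners.

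**The case against.** The strongest reply is that the main treatment contrast is change. The Discussion says so, and a stable additive offset then cancels provided each patient returns to the same machine. The site structure implies this, but the text does not say it. The regressions on brain change benefit in the same way. This stands, and it limits the point to comparisons of levels.

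Second, a reader might infer that scanner differences bias the acupuncture-versus-sham comparison. The documents do not support that. Allocation is random, so any imbalance in scanner is chance imbalance, and the unadjusted residual variance already contains the scanner variation. The loss is precision.

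Third, the sites share vendor, field strength, a 32-channel coil and imaging parameters, which makes offsets of 1 SD or more less likely. No offset, site split or MRI effect size is given, so the figures above are ranges on assumptions. They also describe a single uncorrected test, and so give the error rate or power of no planned MRI analysis. This stands as well.

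Fourth, the missing DTI covariate alone could be put down to a condensed article. That is fair for DTI, but not for the gray-matter and fMRI models, whose covariates are stated.

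**Conclusion.** The point holds for MRI levels compared between patients: arms at baseline, any gray-matter or DTI level contrast between arms, and the MoCA-K halves. Between randomised arms, at an assumed even site split, offsets of 0.5 and 1.0 SD cost 6% and 25% in variance, with no bias in expectation. Confounding is a risk mainly in the MoCA-K split, and only if severity differs by site; at a 40-point imbalance the uncorrected 5% error becomes about 6%, 10% or 24% for offsets of 0.25, 0.5 or 1.0 SD. Paired, change-score and brain-change regression results are exposed only under the conditions in step 5.

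A reader might go further and conclude that the primary result is at risk, or that site must join the DST model, which uses "baseline score with strata factors (such as sex and age) as the covariate". The scanner evidence supports neither: DST is not an MRI measure, and its analysis and sample size are untouched. The change is a cheap improvement that should be made; the trial's main conclusion does not depend on it.

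**What to change.** - Add scanner/site as a nuisance regressor in the between-subject voxel-wise models (VBM, task fMRI, connectivity, and the DTI design in Randomise), in the whole-brain regressions, and in the low/high MoCA-K comparison.
- State that each patient is rescanned on the same scanner at follow-up.

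The cost is analysis wording and one degree of freedom per model. With 50 patients and a model holding an intercept, arm, linear age and sex, residual degrees of freedom go from 46 to 45. Each patient's site is known, and because enrolment is under way, adjusting in the analysis avoids changing the strata. Settling this before the arms are unblinded keeps it from being a post hoc choice.

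### The MRI analysis text does not tie the between-arm gray matter and DTI tests to change from baseline, although the Discussion says change is what will be compared

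*Protocol article*

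**What the plan says.** The Statistical analysis section of the protocol article handles MRI outcomes separately from the clinical scores and says that their comparisons are done differently. Clinical post-test scores get an ANCOVA with the baseline score as covariate.

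- **Gray matter:** a voxel-wise linear model will be used to "compare gray matter volumes within and between groups while controlling for age and sex".
- **DTI:** "The DTI metric maps will be statistically compared within and between groups using a non-parametric permutation test with 5000 permutations".
- **fMRI between groups:** in a sentence that likens the approach to that for gray matter, "functional connectivity from the resting state fMRI at baseline will be assessed between groups".
- **fMRI over time:** "fMRI metrics between baseline and post-treatment will be compared using the paired samples" t test.
- **Regression:** whole-brain models will "test association between metrics of cognitive function and changes in brain function and structure".

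The Discussion states the aim for these data. It says "we will compare changes in MRI metrics between the acupuncture group and sham acupuncture group" and, among the limitations, that "our trial focuses on investigating acupuncture-induced functional and structural brain changes".

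**The concern.** The aim is a difference between arms in change, but the analysis text never specifies that contrast for brain structure. It names volumes and maps as the things compared. For gray matter it lists age and sex as covariates and leaves out the baseline value. Baseline adjustment cannot simply be carried over from the clinical ANCOVA, because the section says that MRI comparisons are handled differently. The authors do write of change when they describe the regressions, so its absence from the between-arm tests is noticeable.

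Two things are at stake. First, an analyst who follows the text could run a post-treatment comparison that leaves stable anatomical differences between people in the error term. By analogy with the fMRI sentence, the analyst could even run a baseline comparison, which says nothing about treatment. Second, the within-arm tests do not fill the gap: a significant change in one arm and a non-significant one in the other is not a test of the difference between arms. An open contrast also allows a choice among baseline, post-treatment and change comparisons once the maps have been seen.

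**Working it through.** **The plan's own figure.** The documents give no power, SD or effect size for any MRI measure. The only sample size figure is for the Digit Span Test: difference 0.87, SD 0.89, two-sided 5%, 90% power. The normal approximation gives n per arm = 2 × (1.960 + 1.282)² × 0.89² / 0.87² = 21.99, so 22 per arm and 44 in total, as stated. With 10% dropout, 22 / 0.9 = 24.4, so 25 per arm and 50 in total, also as stated. This fixes the number of patients available for MRI but gives no power for it.

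**Inputs for the MRI check.** From the protocol: 22 evaluable or 25 enrolled per arm, two-sided 5%, scans at baseline and after treatment. Assumed: equal variance at both times, and a baseline-post correlation r between 0.3 and 0.98, because the documents give none.

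**Formulas.** With the SD of a single-time value set to 1, the between-person variance is:

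- post-treatment value: 1
- change: 2(1 − r)
- post-treatment value adjusted for baseline: 1 − r²

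At 22 per arm, a change test has 80% power (noncentral t) at an effect of 0.865 SD of change. In single-time SD units this is δ = 0.865 × √(2(1 − r)). Power of the other two tests is then computed at the same δ.

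**Worked case, r = 0.9.** δ = 0.865 × √0.2 = 0.387. For the post-treatment test the noncentrality is 0.387 × √(22/2) = 1.28, and power is 24%. With baseline adjustment the standardised effect is 0.387 / √0.19 = 0.89, and power is 82%.

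| r (assumed) | δ at 22 per arm | change test | post-treatment test | baseline-adjusted test |
|---|---|---|---|---|
| 0.3 | 1.023 | 80% | 91% | 94% |
| 0.5 | 0.865 | 80% | 80% | 90% |
| 0.7 | 0.670 | 80% | 58% | 86% |
| 0.8 | 0.547 | 80% | 43% | 84% |
| 0.9 | 0.387 | 80% | 24% | 82% |
| 0.95 | 0.273 | 80% | 14% | 81% |
| 0.98 | 0.173 | 80% | 9% | 80% |

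From r = 0.5 upward, the powers at 25 per arm are the same to the nearest percent.

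**Validity check by simulation** (20,000 trials, 25 per arm, r = 0.95). With no effect, the post-treatment and change tests each reject 4.9% of the time. With a true effect of 0.2 single-time SD, the mean contrast is 0.198 for the post-treatment test and 0.199 for change. Power is 11% and 59% respectively. A baseline comparison rejects 5% of the time, which is its significance level.

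All of this is for one unadjusted test. The plan is voxel-wise with FDR or family-wise correction, so the table shows the relative cost of the contrast and does not give the power of the planned maps.

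**The case against.** The best defence is that the text is silent on whether levels or changes are compared. A two-arm, two-time comparison of change fits the wording, and the Discussion, which says that changes will be compared, may simply complete it. Design matrices are also commonly left to a full protocol or analysis plan, and the DTI sentence follows a stray fragment, so little should be read into its lack of covariates. Much of this stands: the intention is probably change. It does not dispose of the point. The text that is given departs from baseline adjustment, lists covariates without baseline for gray matter, and names baseline as the only time for a between-group MRI test. The article's two sections need to agree whatever an unseen document says.

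Three stronger readings are tempting, and the documents do not support them.

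- *The plan compares levels.* A reader might infer this, but the text says neither level nor change.
- *The wrong null is tested.* Under randomisation a post-treatment comparison has the same expected contrast and the same null as a change comparison, as the simulation shows. It is less precise when r exceeds 0.5, but it is not wrong. Only a baseline comparison, or one that pools the two times, would miss the question.
- *Most of the power is lost.* That needs r above roughly 0.8. Such a value is plausible for brain structure measured 12 weeks apart, but the documents do not give it. At 0.5 nothing is lost against a change test, and below 0.5 the post-treatment test does better than change.

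**Conclusion.** The point holds as an unresolved mismatch between sections. As written, the Statistical analysis section contains no between-arm test of structural change, although the Discussion says that changes in MRI metrics will be compared between arms.

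The cost depends on how the text is carried out. It is nil if change is analysed. If a post-treatment comparison is run, the cost against a change test runs from none at an assumed correlation of 0.5 to 22 percentage points at 0.7 (80% against 58%) and 66 points at 0.95 (80% against 14%). If baseline is compared, the test carries no information on treatment. These sizes rest on the assumed correlation, on equal variances and on a single unadjusted test.

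The MRI outcomes are secondary and were not the basis of the sample size. The primary Digit Span analysis is baseline-adjusted and is unaffected. The matter is still worth correcting, because the neurological mechanism is one of the trial's two stated aims.

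**What to change.** In the MRI part of the Statistical analysis section, state three things:

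1. The between-arm test for gray matter volume and for each DTI metric is run on post-treatment maps with the voxel's baseline value as covariate, keeping age and sex. Post-minus-baseline difference maps are an acceptable alternative. Baseline adjustment is the better default because, in the table above, its power is at least that of either other test at every correlation.
2. Any claim of acupuncture-induced structural change rests on this between-arm test. Within-arm comparisons are descriptive.
3. Any between-arm comparison of baseline maps is labelled as a description of the arms at entry.

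The cost is a few lines of analysis text and, for difference maps, one subtraction per map. Both scans are already scheduled, and no patients or procedures are added. The wording should be fixed before the maps are compared by arm.
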